### Data management

The Data Protection Official at St. Olavs Hospital has approved the data management plan for this study. Data from several sources are collected: (1) therapist referral sheet with background information, (2) blood samples, (3) baseline interviews of participants, (4) participant pen-and-paper self-report and (5) register data. To secure anonymity, participants are given a non-identifiable study ID at randomization. This ID is used throughout the study for data storage and analysis.

Treatment in both arms is delivered in accordance with routines at the clinic and the intervention under investigation is considered low risk. As there are no anticipated detrimental effects or concerns over patient safety associated with this study, a data monitoring committee, interim analyses or stopping guidelines are not considered necessary. As part of routine care, all potential adverse events will be taken care of by the participant’s individual therapist and will, in accordance with hospital policies, be reported to the head of the clinic.

### Statistical methods

The efficacy of the group intervention will be evaluated on an intention-to-treat basis comparing the two arms (SST and TAU). The main efficacy analysis will pertain to the data obtained at post-treatment and 8 months follow up, using *t* tests or mixed models to test for differences in changes in the primary outcome scores from pre-treatment to post-treatment. Baseline characteristics will be tabulated by treatment modality. Per-protocol analyses will also be run.

We will use explorative mediation analyses to investigate whether posttraumatic cognitions influence the outcome measures. We will also consider longitudinal analysis of individual growth curves or analysis of mixed linear models as appropriate.

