### Assessment

Prior to randomization, participants undergo a baseline assessment package (T1). This includes self-reports, a short interview and collection of blood samples. Subsequently, self-report data are collected in both conditions when the group intervention reaches the halfway mark approximately 4 months after baseline (T2; mid-treatment), approximately 4 weeks after the course has ended i.e., 8 months after baseline (T3; post-treatment), 6 months after the end of the group intervention i.e., 13 months after baseline (T4; follow up) and 12 months after the end of the intervention i.e., 19 months after baseline (T5; follow up). The collection of blood samples and a short interview will be repeated at post-treatment and the individual therapist will answer a set of questions at the end of the intervention (T3).

Questionnaires are sent to participants by mail and returned either by mail or by personal delivery to the clinic. Participants who fail to return the questionnaires are contacted a maximum of twice, either by sending another copy of the questionnaire and/or by phone.

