### Primary outcome

The primary outcome is change in the personal recovery experienced from pre-treatment to post-treatment and follow up measured by the Questionnaire about Process of Recovery (QPR) [49]. The scale was originally developed in collaboration with service users, and has been widely used to capture peoples’ accounts of recovery from severe mental illness. Participants are asked about aspects of recovery that are meaningful and relevant to a broad range of patients. In line with the definition of personal recovery, the items capture “a process of changing one’s attitudes, values, feelings, goals, skills, and/or roles. It is a way of living satisfying, hopeful and countering life even with limitations caused by illness” [69]. The 15-item version has been recommended for use both in routine clinical work and in research, and it is scored on a 5-point scale from 0 = disagree strongly to 4 = agree strongly). The psychometric properties in terms of internal consistency, test re-test reliability and convergent validity were found to be high [42].

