### Sample size

To the best of our knowledge, there are no established parameters for reliable and/or clinically significant change in the main outcome measure of this study, the QPR-15. We determined the minimal effect size that would be clinically meaningful to be Cohen’s *d* = 0.5; given the costs of implementing SST groups, a smaller effect size would be of little interest to the clinic. Given α = 0.05 and statistical power of 0.80, we calculated that the trial requires a total of 126 participants, 63 in each arm. Accounting for drop-out, which was 20% in the pilot testing of the group intervention, we plan to enrol a total of 160 participants, 80 in each arm. Several of our secondary outcome measures, e.g. the Work and Adjustment Scale (WSAS) are widely used. Three studies utilizing the WSAS comparing new treatments with TAU identified a mean change between the intervention group and TAU from 4.04 [54], 4.5 [55] and 4.6 [21]. These give a mean score of 4.38. The mean standard deviation for pre-treatment and post-treatment scores was 8.5. A power calculation with α = 0.05 and statistical power of 0.80 requires a total sample of 120, which is in line with our first sample size calculation. The estimations are further in line with general recommendations of 75 persons in each arm for studies with two active arms [1].

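### The primary time point for QPR is stated inconsistently: the analysis text cites an 8-month follow-up that the schedule does not contain, and the outcome definition adds follow-up without naming a visit

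*Protocol article*

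**What the plan says.** Three sections of the protocol article bear on when the primary outcome is assessed.

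- **Assessment** sets the schedule. The post-treatment visit is "8 months after baseline (T3; post-treatment". The first follow-up is "6 months after the end of the group intervention i.e., 13 months after baseline (T4; follow up". The second, T5, is 19 months after baseline and 12 months after the group ends. T2, at about 4 months, is a mid-treatment measurement.
- **Primary outcome** defines the endpoint: "The primary outcome is change in the personal recovery experienced from pre-treatment to post-treatment and follow up", measured by the QPR. No visit is singled out.
- **Statistical methods** states "The main efficacy analysis will pertain to the data obtained at post-treatment and 8 months follow up". The method is t tests or mixed models, used "to test for differences in changes in the primary outcome scores from pre-treatment to post-treatment".

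The **Sample size** section treats the primary comparison as one test: "Given α = 0.05 and statistical power of 0.80, we calculated that the trial requires a total of 126 participants, 63 in each arm", for a Cohen's d of 0.5.

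**The concern.** A primary outcome needs an identifiable time point, and here the sections do not agree on one. The analysis sentence joins post-treatment and an 8-month follow-up as if they were two occasions, which the schedule does not support. Its closing clause names one contrast, ending at post-treatment. The outcome definition reaches further, into follow-up, and the schedule gives that label only to T4 and T5. The text can therefore be read as having one primary time point (T3), two (T3 and a follow-up that cannot be identified) or three (T3, T4 and T5).

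This matters because the trial is not blinded and the primary outcome is self-reported. If the group effect differs between the end of treatment and a year later, either result could be presented as the primary one by citing a different section. Fixing the visit beforehand removes that choice.

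**Working it through.** **Step 1. Look for the 8-month follow-up on the schedule.** The Assessment section places T3 about 4 weeks after the course, T4 6 months after it and T5 12 months after it. These correspond to 8, 13 and 19 months after baseline. The end of the group is then near month 7 on each line: 8 months less 4 weeks, 13 − 6 = 7 and 19 − 12 = 7.

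| Clock for 8 months | Months after baseline | Visit there |
|---|---|---|
| From baseline | 8 | T3, which is post-treatment |
| From the end of the group | 7 + 8 = 15 | none |
| From T3 | 8 + 8 = 16 | none |

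No clock gives a follow-up visit distinct from T3.

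**Step 2. Reproduce the sample size.** Inputs from the Sample size section: d = 0.5, α = 0.05, power 0.80, 20% drop-out. Sidedness is not stated.

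- Formula: n per arm = 2(z for α + z for power)² / d².
- Two-sided: 2 × (1.960 + 0.842)² / 0.25 = 62.8, so 63 per arm and 126 in total, as stated. The exact t-test gives 63.8, so 64 per arm, which is close enough.
- One-sided: 2 × (1.645 + 0.842)² / 0.25 = 49.5, so 50 per arm and 100 in total, which does not match.
- Drop-out: 126 / 0.8 = 157.5, so 158, rounded up to 160.

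The stated N is thus one two-sided comparison at an undivided 0.05, with power 80.1% at 63 per arm.

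**Step 3. Error rate under each reading.** If only T3 is tested, it is 5%. If any one of k visits could carry the claim, each at two-sided 0.05, the upper reference is independence: 1 − 0.95² = 9.75% for k = 2 and 1 − 0.95³ = 14.3% for k = 3. Contrasts at different visits in the same people are correlated. The protocol gives no correlation, so a range is assumed. Simulating k equally correlated normal statistics (1,000,000 draws each) gives P(any |Z| > 1.96):

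| Assumed correlation | k = 2 | k = 3 |
|---|---|---|
| 0.5 | 9.1% | 12.5% |
| 0.7 | 8.3% | 10.9% |
| 0.8 | 7.8% | 9.8% |
| 0.9 | 7.0% | 8.4% |

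**Step 4. Price of keeping several visits primary with an equal α split.** Power = Φ(d√(n/2) − z), with d√(n/2) = 0.5 × √31.5 = 2.806 at 63 per arm.

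- k = 2, α = 0.025, z = 2.241: Φ(0.565) = 71.4%. For 80% power: 154 evaluable, 154 / 0.8 = 192.5, so 193 enrolled.
- k = 3, α = 0.0167, z = 2.394: Φ(0.412) = 66.0%. For 80% power: 168 evaluable, 168 / 0.8 = 210 enrolled.

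**The case against.** The best defence is that the 8-month phrase is a clumsy second label for T3. T3 is the 8-month visit, the sentence ends with a single contrast up to post-treatment, and the sample size fits a single test. On that reading there is one primary test, and the error rate is 5%. The Primary outcome section could then be describing the period over which QPR is measured, without making T4 and T5 tests of the main hypothesis.

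Much of this stands. A reader might infer that the protocol plans several primary tests at an unadjusted 5%, or that any significant visit counts as success. The document says neither. The analysis sentence also allows mixed models. One joint test over visits, or a rule that all visits must succeed, would not inflate the error. How α is shared across visits is commonly left to an analysis plan, which is not shown here, so the absence of such a rule is not the point.

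What the defence does not remove is the inconsistency. Even if the 8-month phrase means T3, the analysis sentence lists one occasion as two, and the outcome definition still includes follow-up while the tested contrast stops at post-treatment. An analysis plan could not follow both sections as written.

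**Conclusion.** The primary time point is wrong as written and should be corrected. This conclusion rests only on comparing the Assessment, Primary outcome and Statistical methods sections, and it holds under the most favourable reading of the 8-month phrase.

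The consequence for type I error is conditional. It is 5% if T3 alone is tested. It is about 8–9% for two visits and 10–13% for three if any one may carry the claim at 5% each, with correlations assumed between 0.5 and 0.8. These figures illustrate what the loose wording could permit. They do not measure a stated plan, and the documents do not support saying that the error rate is uncontrolled. The two-visit figure is also hypothetical in that the second visit cannot be identified from the text. The sample size is sound for a single primary visit.

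**What to change.** Name one primary visit, identically in both sections. T3, 8 months after baseline, is the natural choice because it matches the contrast already in Statistical methods and the single-test sample size.

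- **Statistical methods:** drop the reference to an 8-month follow-up. State that the main analysis compares SST with TAU on change in QPR-15 from T1 to T3, two-sided α = 0.05.
- **Primary outcome:** reword so that change to T3 is primary, and change to T4 and T5 is secondary.

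Testing T4 and then T5 in fixed order after a significant T3 is optional. Reporting them with confidence intervals would also do.

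If the sponsor wants follow-up visits to stay primary, list them by visit and state one joint test, an α split or a fixed testing order. An equal split lowers power as shown above unless more participants are enrolled.

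With T3 as the single primary visit, the cost is two reworded sentences and the loss of primary status for T4 and T5. No new data are needed, and N = 160 is unchanged. The registry entry was not available here. It should be checked for the same wording and aligned if needed.

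### The main QPR analysis may be a t test or a mixed model with no rule for choosing; the change-score t test should be deleted and one baseline-adjusted repeated-measures model named

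*Protocol article*

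**What the plan says.** Statistical methods in the protocol article states the analysis basis: "The efficacy of the group intervention will be evaluated on an intention-to-treat basis comparing the two arms". The next sentence sets the time frame, "The main efficacy analysis will pertain to the data obtained at post-treatment and 8 months follow up", and the method: *t* "tests or mixed models to test for differences in changes in the primary outcome scores from pre-treatment to post-treatment". Nothing says which of the two methods is primary or what would decide it. Mixed models come up once more at the end of the section, again as an option: "We will also consider longitudinal analysis of individual growth curves or analysis of mixed linear models as appropriate".

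Primary outcome defines the endpoint as a change: "The primary outcome is change in the personal recovery experienced from pre-treatment to post-treatment and follow up". Assessment schedules self-report at five points: baseline (T1) and about 4, 8, 13 and 19 months later (T2 to T5). T3, the post-treatment visit, is the 8-month one. Trial design says that participants, therapists and researchers are not blinded to allocation. Randomization stratifies by gender. Sample size asks for 126 participants, 63 per arm, for d = 0.5, and enrols 160 to allow for 20% drop-out.

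**The concern.** Two different analyses are allowed for the primary test. They can give different estimates and p-values, and researchers who know the allocation could choose between them after seeing the results. That alone weakens the primary result.

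The two options are also not equally good. A t test on T1-to-T3 change needs both scores from each participant. Someone who returned T2 but not T3 contributes nothing, although the T2 score carries information about T3. If non-return depends on earlier scores, a complete-case comparison can be biased where a likelihood-based model, under missing at random, is not. A change score also subtracts the whole baseline value whatever the correlation between the two measurements, and this costs precision that baseline adjustment would recover from the same data.

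**Working it through.** **Inputs from the protocol article (Sample size):** d = 0.5, α = 0.05, power 0.80, 63 per arm, 20% drop-out, 160 enrolled. **Assumed:** two-sided test; equal SD σ at T1 and T3; baseline–T3 correlation r of QPR, which the protocol does not give, shown at 0.3, 0.5 and 0.7.

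**1. The plan's own figure.** n per arm = 2(1.96 + 0.8416)²/0.5² = 62.8, so 63 per arm and 126 in total, as stated. The exact t calculation gives 64 per arm. With 20% drop-out, 126/0.8 = 157.5 and 128/0.8 = 160. The planned 160 is reproduced and is not in error.

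**2. Participants left out by the t test.** 160 × 0.20 = 32. Without imputation about 128 of 160 would be analysed.

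**3. Variance.** With outcome SD σ:
- change score: 2(1 − r)σ²
- baseline-adjusted (ANCOVA): (1 − r²)σ²
- ratio, adjusted to change: (1 − r²)/[2(1 − r)] = (1 + r)/2, which is below 1 for every r below 1.

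**4. Power,** taking d = 0.5 in raw-score SD units, 63 analysed per arm, non-central t with non-centrality d*√(63/2). Here d* = 0.5/√(2(1 − r)) for the change score and 0.5/√(1 − r²) for the adjusted analysis.

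| r | Variance ratio | d*, change | Power, change-score t test | d*, adjusted | Power, adjusted |
|---|---|---|---|---|---|
| 0.3 | 0.65 | 0.423 | 0.65 | 0.524 | 0.83 |
| 0.5 | 0.75 | 0.500 | 0.80 | 0.577 | 0.90 |
| 0.7 | 0.85 | 0.645 | 0.95 | 0.700 | 0.97 |

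The table covers baseline adjustment only. It does not count any gain from using T2, T4 and T5 scores of participants who lack T3, and it does not measure bias from non-return, for which the documents give no figures.

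**The case against.** Several stronger readings are tempting, and the document does not support them.

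- *The plan rests on a t test.* It does not: a mixed model is named beside it. The defect is the unresolved choice.
- *The t test ignores baseline.* It does not: a change score subtracts the baseline with coefficient 1. Under randomisation, with complete data, it is a valid test, only a less precise one.
- *The t test contradicts intention to treat.* That goes too far. The phrase can mean analysis by randomised arm, and a t test after multiple imputation would fit it. A missing-data rule may stand in an analysis plan not shown here, and its absence from an article is no fault. What remains is that the t test, as named, has no imputation attached to it.
- *The trial is underpowered.* This does not follow. The protocol does not say on which SD d = 0.5 is defined. If it is the SD of change, the t test has about 0.80 power with 63 per arm whatever r is, and the 0.65 does not arise. The precision ranking still holds, because the variance ratio does not depend on how d is scaled.
- *The supporting WSAS calculation is wrong because it uses the SD of raw scores,* "The mean standard deviation for pre-treatment and post-treatment scores was 8.5", *for a difference in change.* That should not be argued. WSAS is a secondary outcome, and raw and change SDs agree at r = 0.5. Above 0.5 the raw SD is conservative. What the cited differences and SDs represent cannot be checked from the article.

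A further objection concerns the remedy. A mixed model with baseline only as a covariate also drops anyone with no post-baseline QPR. That is correct, and the fix has to allow for it.

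**Conclusion.** The concern holds in this limited form. The protocol leaves the primary method open between two named analyses in an unblinded trial, and one of them is inferior on both counts that matter here. Without imputation the t test omits about 32 of 160 randomised participants at the planned drop-out. At every r below 1 its variance exceeds that of a baseline-adjusted analysis: the adjusted variance is smaller by 35%, 25% and 15% at r = 0.3, 0.5 and 0.7.

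The count of 32 assumes that drop-out means a missing T3 score. The variance figures depend on the assumed r and on equal SDs at T1 and T3. The power figures depend in addition on d being on the raw-score scale. Bias from non-return is possible but cannot be sized from the document. This should be corrected, but it does not invalidate the design or its sample size.

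**What to change.** Delete the t test option and fix one primary analysis before outcome data are examined: a likelihood-based mixed model for repeated QPR measures with arm, visit and arm-by-visit terms, adjusted for baseline QPR and the gender stratification factor, with the between-arm contrast at T3 as the primary test. Naming T3 also settles whether the main time point is one visit or two.

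State how baseline enters, in one of two ways:
- Put T1 in the outcome vector with the arm means constrained equal at T1, so that every randomised participant with any QPR score contributes.
- Use T1 as a covariate, and say plainly that participants with no post-baseline QPR do not contribute.

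The cost is a sentence or two of wording and modest programming. The visits are already scheduled, and neither the 126 nor the 160 needs to change.

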To meet the need for a broad and integrated treatment model for patients with complex PTSD, the Modum Bad Trauma Clinic issued a treatment manual in 2014 named “Tilbake til Nåtid” (“Back to the present” [34];). The group-based treatment approach detailed in this manual uses stabilization and skill training (SST) to increase participants’ affect regulation when exposed to triggers, and to increase their capacity of stabilization or level of tolerance to handle unpleasant reminders. The course, lasting for 2 h per session over 20 weeks, is combined with individual treatment, not specified. The courses have been running at Modum Bad since 2008. A randomized controlled trial has been carried out in this highly specialized setting (results to be published).

Results have been mixed in research on similar treatments. Zlotnic et al. [73] demonstrated a considerable effect in a randomized controlled trial; similarly, a preliminary, non-controlled study in Scotland showed promising results [36]. However, results obtained by Dorrepaal et al. [22] were less clear, with only a non-significant trend towards symptom reduction.

Clinical experience with this particular SST approach is promising, as seen both from two outpatient clinics around Oslo that have implemented the treatment [47] and from our own community mental health hospital, where the course has been completed more than 10 times since 2015. The programme has been well-received by patients and clinicians. In an unpublished evaluation, we collected pre-programme and post-programme data in four questionnaires (Symptom Checklist (SCL-90), Impact of Event Scale (IES), Dissociative Experience Scale (DES) and Somatic Experience Scale (SES)) in the first 33 participants, of whom 18 (56%) completed data collection both at the start and the end of the course. We identified a significant decrease in symptom level. The drop-out rate was acceptable (approximately 20%) and was mostly due to change in occupational or educational status. Overall, feedback on the course, as given by participants and individual therapists, was positive. The systematic evaluations and feedback given by participants at the end of the courses has guided the development of the present research project.

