### Interventions

Participants in both arms of the study continue to receive conventional individual treatment from the therapist to whom they are already allocated. As the study is carried out in a natural setting, the content of this conventional therapy varies and is not standardized in any manner, but information on the content of individual treatment is collected from therapists at post-treatment (T3). The outpatient clinic offers medical and psychological treatment for mental illness. All patients have an individual therapist, in most cases a psychologist or psychiatrist. If the primary therapist is not a psychiatrist or a senior psychologist, one such will be involved in the treatment as supervisor and counsellor. All patients are discussed in treatment teams that include specialists and medical doctors.

Participants in the intervention group will also receive a group-based SST intervention based on the manual “Tilbake til Nåtid” (“Back to the present” [34];), which was developed by clinicians at Modum Bad’s Trauma Clinic, a highly specialized national trauma clinic. The manual is based on work by Boon and colleagues [9] and has been changed and adapted by the Norwegian authors. The manual is intended for use by both the participants and the therapist; it teaches psychoeducation and skills relevant to people with long-lasting trauma reactions. It is based on several theoretical models and also covers everyday routines and knowledge related to somatic and mental aspects. The manual also encourages reflections and discussions among the participants on how to regulate difficult affects and interpersonal difficulties that may arise as a result of triggers from previous traumatic experiences.

The manual is organized into 20 chapters and covers the following topics: (1) introduction and motivation, (2) window of tolerance, (3) understanding PTSD, (4) complex traumatization, (5) dissociation, (6) understanding trauma memories and triggers, (7) coping with triggers, (8) mindfulness, (9) bodily reactions, (10) summary and review of content so far, (11) establishing a daily structure, (12) safe sleep, (13) trauma-related cognitions, (14) reflective skills, (15) understanding emotions, (16) self-compassion, (17) coping with anger, (18) fear of relations, (19) assertiveness and boundaries and (20) evaluation and goodbye for now.

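### Any attendance-based per-protocol set can filter only the SST arm; label that analysis supportive and add a complier average causal effect estimate

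*Protocol article*

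**What the plan says.** The Statistical methods section of the protocol article evaluates efficacy by intention to treat, comparing change in the primary outcome between arms, and then adds: "Per-protocol analyses will also be run". It gives no population, threshold or role for that analysis.

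Under Interventions, both arms keep their individual therapist, and "the content of this conventional therapy varies and is not standardized in any manner". SST participants also attend a manualised group course that meets over 20 weeks. That course is the only component with a schedule against which attendance can be counted.

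On leaving the course, the Background reports from the pilot: "The drop-out rate was acceptable (approximately 20%) and was mostly due to change in occupational or educational status". The Sample size section carries the same rate forward: "Accounting for drop-out, which was 20% in the pilot testing of the group intervention", followed by "we plan to enrol a total of 160 participants, 80 in each arm".

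**The concern.** An attendance rule can be applied in SST but has no equivalent in TAU. Whatever cut-off is chosen, those who fall short leave the SST side, while the TAU participants who would also have fallen short cannot be identified and stay in. If the two kinds of participant would change differently without SST, the contrast mixes that difference with the treatment effect. A later definition of the cut-off does not cure this.

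The reported reason for leaving makes such a difference plausible. Occupational status is a secondary outcome, and the definition of personal recovery under Primary outcome includes goals and roles. The direction is not known: a participant may leave because life is improving or because it is not.

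At stake is the only analysis named in the article that a reader would take as the effect of actually attending SST.

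**Working it through.** **The plan's own figure.** Inputs from Sample size: d = 0.5, α = 0.05 (two-sided), power 0.80. Per arm, n = 2 × (1.960 + 0.842)² / 0.5² = 62.8, so 63 and 126 in total, as stated: "Given α = 0.05 and statistical power of 0.80, we calculated that the trial requires a total of 126 participants, 63 in each arm". For 20% drop-out, 126 / 0.8 = 157.5, so 158 against 160 planned. The sample size is not in dispute.

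**Inputs for the check**
- 80 per arm (Sample size).
- p, the share of SST participants below the attendance threshold: 0.20. This is the pilot's course drop-out rate, used here as an assumption.
- g, the expected change in would-be attenders minus that in would-be non-attenders, without SST, in SD units. It is not in the documents, so a range is shown.
- e, the effect of assignment to SST on those below the threshold, in SD units. It is not in the documents, so a range is shown.

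**Per-protocol bias.** Let attenders change by m without SST.
- Mean in SST attenders: m + effect.
- Mean in all of TAU: (1 − p)m + p(m − g) = m − pg.
- Contrast: effect + pg, so the bias is pg.

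| g | Bias at p = 0.20 | Estimate if the true effect is 0.50 | Type I error if there is no effect |
|---|---|---|---|
| 0 | 0 | 0.50 | about 5% |
| 0.2 | 0.04 | 0.54 | about 6% |
| 0.5 | 0.10 | 0.60 | about 9% |
| 0.8 | 0.16 | 0.66 | about 15% |

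Negative g mirrors this: g = −0.5 gives 0.40. The error rates come from 20,000 simulated trials per row, in which the intention-to-treat test stayed at about 5%.

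A hand check at g = 0.5 agrees. With 64 attenders against 80, the standard error is √(1/64 + 1/80) = 0.168. The shift is 0.10 / 0.168 = 0.60 standard errors, and P(Z > 1.36) + P(Z < −2.56) = 0.087 + 0.005, about 9%.

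At p = 0.30 the biases for g = 0.2, 0.5 and 0.8 are 0.06, 0.15 and 0.24 SD, with type I error of about 6%, 14% and 26%.

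**CACE.** If nobody in TAU receives SST, CACE = ITT / (1 − p). With a true effect of 0.50 in attenders, ITT = 0.8 × 0.50 + 0.2e. The result does not depend on g.
- e = 0: 0.40 / 0.8 = 0.50.
- e = 0.10: 0.42 / 0.8 = 0.525, a bias of 0.025.
- e = 0.25: 0.45 / 0.8 = 0.5625, a bias of about 0.06.

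The per-protocol bias is the larger of the two when |g| exceeds e / (1 − p) = 1.25e, that is 0.125 at e = 0.10 and about 0.31 at e = 0.25.

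**Precision at p = 0.20.** The CACE standard error is √(2/80) / 0.8 = 0.198, against 0.168 for per-protocol. The interval is about 18% wider. The simulation gave SDs of 0.20 and 0.17.

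**The case against.** The strongest objection is that the article never defines the per-protocol set, so the criticism supplies its own version. A condensed article may leave that definition to an analysis plan, and its absence is not held against this one. What stands is narrower: if the set rests on attendance, no choice of threshold avoids the one-sided filter.

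A reader might infer that no TAU participant can be off protocol. The documents do not support that. Content that is not standardised can still be stopped, and TAU participants could be excluded for ending individual treatment, receiving SST, breaching eligibility or missing assessments. Such exclusions do not pick out those who would have skipped SST, however, so they do not restore balance.

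A reader might also infer that the pilot shows course leavers to have a different prognosis. It does not. A new job may simply clash with session times. Because the planned test is on change from pre-treatment, stable differences in level cancel, and g must be a difference in change. That makes the larger values less likely, and at g = 0 there is no bias.

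Finally, CACE might be read as an unbiased answer to the same question. It is unbiased only if assignment has no effect on those below the threshold. That is doubtful in an unblinded trial with a self-reported outcome and a course in which someone just short of the threshold has received real treatment. With e = 0.25 its bias of about 0.06 SD exceeds the per-protocol bias of 0.04 SD at g = 0.2. This part stands, and it is why CACE is proposed as an addition and not as a replacement.

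**Conclusion.** The point holds for any attendance-based per-protocol set: it filters only SST and gives up the randomised comparison. At 20% non-attendance the bias is 0.2 × g, running from zero at g = 0 to 0.16 SD at g = 0.8. The middle case, 0.10 SD, is one fifth of the design effect of 0.5. These sizes rest on an assumed g and on pilot drop-out standing in for non-attendance.

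A reader might conclude that the trial's main result is at risk. It is not: the efficacy evaluation is by intention to treat, and the per-protocol analysis is additional. This is a cheap improvement to a secondary estimate, not a correction to the primary one.

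**What to change.** Label the per-protocol analysis as supportive only, and add:

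> The effect of attending SST will be estimated as a complier average causal effect, with randomised arm as instrument for attending at least a pre-stated number of the 20 sessions, retaining all randomised participants.

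State the assumptions beside it: assignment has no effect on those below the threshold, and no SST is received in TAU. Set a low attendance threshold, or repeat the estimate over several thresholds, because partial attenders may benefit.

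The cost is one sentence, a two-stage regression and a session attendance record for the SST arm, which an attendance-based per-protocol set needs anyway. The interval is somewhat wider than the per-protocol one. Missing outcomes still need their own handling.
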